#### Cost outcomes

All persons involved in programme design, implementation, participation (as a beneficiary), and evaluation will complete cost diary sheets, detailing all the financial (and/or time) costs associated with each activity that they perform. Costs will be divided into the following two components based on the processes necessary to set up and deliver the programme: [1] set-up costs (e.g. initial training costs, and set-up before the start of the programme) and [2] programme delivery costs (e.g. travel to group sessions, room preparation, running the group sessions, room rental for programme delivery, administrative costs, and materials/supplies). Details of costs recorded previously for the cost-effectiveness analysis were presented elsewhere [32]. In addition to these, we will estimate the costs needed to access other social and mental health services available in each implementation site (e.g. by assessing participant use of other mental health services or helpline counselling services for child or parent mental health issues; as well as child emergency room and child welfare services).

*Family poverty* will be assessed with three measures. One measure assesses household assets (numbers of mobile phones and internet access) and is a modified five-item version of the MICS [65]. The current items were included based on previous analyses in each of the three countries that demonstrate what household assets are appropriate to assess (significant variance, accessibility). We will assess participants’ income after covering for the basic expenses with one item, with options ranging from *1 = enough to that I/we can comfortably purchase most of the things we really want* to *3 = not enough to purchase much of anything I/we really want* (i.e. after paying for essential expenses like food, housing, utilities, child care, and medical care). *Family hunger* will be assessed with the Food Insecurity Experience Scale [66]. The FIES consists of eight items with a dichotomous response pattern (“*yes*”/”*no*”) and a “*don’t know*” option [66].

*Impact of COVID-19 pandemic* will be assessed with three ordinal items targeting (a) the amount of stress felt by the parent because of COVID-19; (b) the extent of the (potential) negative impact that the pandemic has had on the child; (c) the extent of the (potential) negative impact of COVID-19 on the family.

*Parents’ exposure to adversity* and *maltreatment* during the first 18 years of life will be assessed with the Adverse Childhood Experiences Questionnaire (ACE-Q), a ten-item scale (each item with a “*yes*” or “*no*” response option) tapping into emotional and physical abuse, physical neglect, and abuse related to atypical households [67]. A modified version of the Child Abuse Screening Tools Retrospective version (ICAST-R) [68] will comprise three items to assess the history of physical maltreatment and verbal abuse.

There will be a short version for the assessment of the secondary caregivers. This comprises the CABI, parenting stress, positive parenting, parental couple satisfaction, and alcohol misuse.

### Data management and data analysis plan

#### Data management plan

The University of Klagenfurt is responsible for monitoring data collection, ensuring data quality, planning statistical analyses, and keeping the rest of the steering committee informed on the progress of these activities.

Survey and audio data collected electronically will be anonymised (participants are identified through numerical codes) and uploaded weekly to a central secure data server at Klagenfurt University. Access to the data will be granted only to the members of the research team. Electronic equipment used for data collection (tablets, audio-recorders) will be password-protected and kept in a locked cabinet when not in use. Paper versions of questionnaires, adverse events forms, informed consent sheets, identification sheets and other hard copy documents used in data collection will be archived by researchers and stored safely by the local teams in the country of the data collection. De-identified adverse event forms will be shared with ethical oversight teams from the Universities of Bremen and Klagenfurt. All electronic and paper data will be kept by each site for ten years, in accordance with the Code of Conduct at the University of Klagenfurt (https://www.aau.at/en/research/research-profile/good-academic-practice/).

#### Data analysis

##### Sample size calculation

To allow detection of small effect sizes, we will estimate sample size based on a *d* = .25 (*f* = .10) for the primary outcomes. Detecting this effect in a repeated measures ANOVA at an alpha of .05 whilst ensuring a power of 80% requires a total sample of *N* = 704. We will examine the change in the primary outcomes across three time points (pre, post, and follow-up) within the overall sample using latent growth modelling and conduct a multi-group analysis to test differences across countries. To reach the required sample size of 704, we will recruit a total of 864 families for baseline assessment, assuming approximately 17% drop-out rate based on our previous phase of data collection [69].

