## Methods

### Study design

We aim to recruit 864 primary caregivers of children aged 2 to 9 years old from North Macedonia, Romania (both classified as upper middle-income countries; the World Bank categorised Romania as high-income country based on 2019 per capita income for the first time) and Republic of Moldova (lower middle-income country; *n* = 288 per country). Participants will be randomly allocated to one of the two parallel study arms: control group (consisting of a lecture) or a parenting intervention group receiving a five-session PLH-YC programme.

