#### Group allocation and allocation concealment

Prior to randomisation, all countries will identify and select a sample of recruitment sites (schools, kindergartens, community, and social services centres) covering different neighbourhoods, geographical areas, ethnic compositions, and socio-economic strata in and around Skopje (North Macedonia), Cluj-Napoca (Romania), and Chișinău (Republic of Moldova).

Randomisation will be coordinated by one of the project partners (University of Klagenfurt) using an online randomiser, https://www.randomizer.org/ (*N* = 288 per country, 864 in total). Participant numbers will be randomised to the PLH-YC programme or the control condition after completion of the baseline assessment based on the randomisation list (individual 1:1 randomisation in blocks of 24). The randomisation list will be provided to the team in Bremen, who will be contacted after each participant is enrolled to unveil their assignment. This threefold procedure allows the analysis team to remain blind to group assignment, ensures that assignment occurs independently and ensures that teams in each country receive allocation information after enrolment.

Participants will be allocated to groups after completion of the pre-assessment. Thus, outcome assessors and participants will be blinded to group allocation at pre-assessment. All data assessors conducting pre-test, periodic, post-test, and follow-up interviews with parents will be blinded regarding the allocation of participants to the groups to minimise evaluation bias: The implementation of the intervention will be conducted by different staff (programme coordinators and facilitators) than the assessments. Thus, data assessors will be unaware of the group allocation of participants at the later assessment points (periodic, post, follow-up). To ensure that participants do not reveal their group allocation during the post- and follow-up assessment to the assessor, the data assessor will ask the participants to not share the group allocation at the beginning of the interview. Only in cases where the parent reports a (serious) adverse event, will the group allocation be unblinded (during periodic  and follow-up assessments). Upon completion of the pre-test measurements, caregivers will be notified of their allocation status.

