### Study outcomes

#### Primary outcome

*Child aggressive behaviour* will be assessed with the respective subscale of the parent-report Child Behavior Checklist (CBCL) 1½–5 and 6–18 years old [43]. Parents rate the occurrence of certain behaviours of their child on a 3-point Likert Scale (0 = *not true* to 2 = *very true* or *often true*).

*Child externalising disorders* will be evaluated by using The Mini International Neuropsychiatric Interview for Children and Adolescents – Parent Version (MINI-KID-P) [44]. The MINI-KID-P will be used to assess whether the criteria (based on ICD-10 and DSM-5) for (a) Conduct Disorder (CD) (F91.1, F91.2, F91.9) or (b) Oppositional Defiant Disorder (ODD) (F91.3) are met (yes/no). The results of the two disorders will be combined to one binary total score with 0 = *no externalising disorder* and 1 = *current externalising disorder* (ODD or CD).

On three occasions between baseline and post-test assessments, Parent Daily Ratings (PDR) [45] will be used to monitor *child oppositional and aggressive behaviour problems* that occurred within the last 24 h (answer format: *did occur/did not occur*). In order to minimise drop-outs, we will only administer the oppositional and aggressive subscale (10 items + 2 positive items) instead of the full PDR. We excluded the last item from the subscale (“he/she pouts”) because this question caused translation problems in the three implementation countries. The item was not understood correctly by parents and assessors and thus did not result in valid answers. The PDR will be assessed over the phone three times between pre- and post-assessment.

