##### Primary and secondary outcome analyses

Data will be analysed using an intention-to-treat approach, in line with the study protocol and with good practice in RCTs [70]. Missing data will be handled using either multiple imputation or Full Information Maximum Likelihood (FIML) method [71].

The primary analysis will consist of testing comparatively the magnitude of change in child aggresive behaviour, in the control vs. PLH-YC participants, at post-test and follow-up. Identical analyses will be run for the secondary outcomes (i.e. child internalising problems, dysfunctional parenting strategies, positive parenting, daily reports of effective parenting behaviour, child maltreatment, parental mental health, IPV, couple satisfaction, parenting stress, quality of parent-child relationship, and child ’s quality of life). The main analyses will involve testing pre-post or pre-follow-up differences controlling for pre-intervention levels whilst accounting for covariates. Maximum likelihood estimation with robust statistics will be used with Mplus 8.2 software to account for non-normal distributions in measures and also apply a FIML framework for handling missing data at post- or follow-up. The models will be further tested using latent growth curve models adjusting for country and pre-assessment levels of the outcome variables (e.g. age as a time-invariant covariate). Indirect effect models will be tested in a structural equation framework and include participation rate and fidelity as mediators for the PLH-YC group and enrolment rate as the mediator across groups. In additional analyses, we will also model the effects of participation (i.e., attendance). This will be analysed with Complier Average Cause Effect models that estimate the magnitude of the paths based on the baseline scores in predictors (e.g. family adversity) and actual participation [72]. Further clustering will be within groups (facilitators) and included in subsequent analyses as needed. The analyses for MINI-KID ODD/CD positive screen will be conducted with logistical regression models due to the categorical nature of the data. Depending on the distributions and on other descriptive indicators, Bayesian analyses will be used as deemed appropriate.

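### The planning effect is printed as d = .25 (f = .10), but with two equal arms these are two different effects, so the effect behind N = 704 and 80% power is undefined

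*Protocol article*

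**What the plan says.** The section on sample size calculation in the protocol article gives the planning effect: "we will estimate sample size based on a *d* = .25 (*f* = .10) for the primary outcomes". The required size is then introduced by "Detecting this effect in a repeated measures ANOVA at an alpha of .05 whilst ensuring a power of 80% requires a total sample of *N*", and the figure given there is 704. The section does not say whether the ANOVA tests arms, time or arm by time, how many measurements enter it, or what correlation between them is assumed. Three time points are mentioned only for the latent growth model in the next sentence.

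The design section states "Participants will be randomly allocated to one of the two parallel study arms", and the section on allocation states "individual 1:1 randomisation in blocks of 24".

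The section on primary and secondary outcome analyses describes the main test: "The main analyses will involve testing pre-post or pre-follow-up differences controlling for pre-intervention levels whilst accounting for covariates".

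The section on the primary outcome lists, beside the CBCL aggression score, a MINI-KID diagnosis of oppositional defiant or conduct disorder: "The results of the two disorders will be combined to one binary total score". This outcome is to be analysed by logistic regression.

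**The concern.** Cohen's f and d are tied by a fixed rule once the number of arms and the allocation ratio are known. Here both are known, and the printed pair breaks the rule. The required number of families and the power both rest on that pair. Required size varies with the inverse square of the effect, so moving from .25 to .20 raises it by a factor of (.25/.20)² = 1.56.

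What is at stake is interpretation. Someone who later reads a null result, or a small significant one, needs to know which effect the trial was built to detect with 80% power. The article gives two answers. It also attaches the claim to the primary outcomes in general, although one of them is binary and a repeated measures ANOVA does not size it.

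**Working it through.** **Inputs from the protocol article.** d = .25 and f = .10, printed as equal; alpha .05; power 80%; N = 704 (sample size calculation); two arms (study design); 1:1 (allocation). Two-sided tests are used. Every correlation r below is an assumption, because the article gives none.

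**1. Conversion.** With two equal arms the means lie d/2 either side of the grand mean in SD units, so f = d/2.
- d = .25 gives f = .125.
- f = .10 gives d = .20.

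**2. Unadjusted two-arm comparison.** N ≈ 4(1.960 + 0.842)²/d² = 31.4/d².
- d = .25: 31.4/.0625 ≈ 502; exact noncentral t gives 506.
- d = .20: 31.4/.04 ≈ 785; exact gives 788.
- Exact power at 704: 91% for d = .25 and 75% for d = .20.

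**3. Repeated measures ANOVA, between-arm effect.** Noncentrality λ = f²·N·m/[1 + (m − 1)r], with m waves and 1 and N − 2 degrees of freedom. Take m = 3 and r = .5, so λ = 1.5·f²·N.
- f = .125: N = 338.
- f = .10: N = 526.

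**4. Trying to reproduce 704.** Two routes reach it or come close, each with r left free.
- Between-arm effect, f = .10, m = 3, r = .84: λ = .01 × 704 × 3/2.68 = 7.88, and the required N is exactly 704. With r = .80 it is 684; with r = .85 it is 710. This route keeps f and gives up d = .25.
- Pre-post change with d = .25 and r = .30: the SD of change is √(2 × .70) = √1.4, so N ≈ 502.3 × 1.4 = 703.3, or 704 when rounded up. The exact figure is 706. In this two-by-two layout the interaction f is d/4 = .0625. This route keeps d and gives up f = .10.

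Neither route restores the sentence as printed. Because r was chosen to hit the target, neither shows what was actually done.

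**5. The planned baseline-adjusted contrast.** Adjustment for baseline multiplies the residual SD by √(1 − r²), so N falls by the factor 1 − r². Exact results:

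| Assumed r | N for d = .25 | N for d = .20 | Power at 704, d = .25 | Power at 704, d = .20 | Smallest d with 80% power at 704 |
|---|---|---|---|---|---|
| 0 | 506 | 788 | 91% | 75% | .21 |
| .30 | 460 | 718 | 93% | 79% | .20 |
| .33 | 450 | 702 | 94% | 80% | .20 |
| .50 | 380 | 592 | 97% | 86% | .18 |

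The last column follows from d ≈ 2.80 × √(4/704) × √(1 − r²) = .211 × √(1 − r²).

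So 704 is not the 80% requirement for d = .25 under this analysis at any correlation, since the maximum is 506. For d = .20 it is the requirement only near r = .33.

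**The case against.** The strongest reply is that a repeated measures ANOVA has no single required N until the tested effect and the correlation are fixed, and that a journal article may leave both to a fuller document. That stands. A reader might infer from the mismatch that 704 follows from neither effect and that 80% is wrong for both. The document does not support this: step 4 reaches 704 exactly for f = .10, and 706 for d = .25 as pre-post change. What does not stand is using the missing detail to excuse the printed pair, because no choice of correlation makes d = .25 and f = .10 the same effect in two equal arms.

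A reader might also infer from the 75% in step 2 that the trial is underpowered. That figure is for an unadjusted test. At an assumed r of .5 the planned adjusted test has 97% and 86% power, above 80% for both effects.

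Sizing on a simpler test than the final model is common practice and is not in itself an error. It is also fair that the analysis section defines the primary analysis through child aggressive behaviour, which is continuous. But the sample size sentence speaks of primary outcomes in the plural, and the binary diagnosis is listed among them.

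The dropout statement ("assuming approximately 17% drop-out rate based on our previous phase of data collection") may look wrong, since 704/864 = 81.5% implies 18.5% loss. It is not an error: 704/.83 = 848.2, or about 283 per country, and rounding up to full blocks of 24 gives 12 × 24 = 288 per country and 864 in all. A loss of power from group clustering could be argued too, but its size would rest on design effects that the article does not give, so it is not claimed here.

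**Conclusion.** The effect size statement contradicts itself. This follows from the two-arm 1:1 design alone and needs no assumption. The two readings differ materially: 506 against 788 families unadjusted, or 338 against 526 in a three-wave between-arm ANOVA at an assumed r of .5. The figure 704 cannot be verified from what is printed, but it is not shown to be wrong.

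For the baseline-adjusted contrast, 704 is more than d = .25 needs at any correlation, and it matches d = .20 only near r = .33. The direction of any power error therefore depends on which effect was meant and on r, and the article settles neither. Nor does it show whether d or f was the value actually used.

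The 80% claim cannot be carried over to the binary MINI-KID outcome. Any power figure for that outcome would need a prevalence that the article does not state.

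**What to change.** Rewrite the sample size paragraph so that it:
- states which effect was used, with its correct conversion: either d = .25 (f = .125) or d = .20 (f = .10). This is for the sponsor to establish from its own calculation;
- names the effect tested in the repeated measures ANOVA, the number of waves and the assumed correlation, so that 704 can be reproduced or corrected;
- restates, for the baseline-adjusted contrast on CBCL aggression, the power at 704 completers and the smallest effect with 80% power, with the correlation assumed;
- limits the 80% power claim to the continuous outcome.

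The cost is one paragraph and one recalculation. The trial status section reports recruitment as complete; the target of 864 does not change and no further families are needed.

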##### Primary and secondary outcome analyses

Data will be analysed using an intention-to-treat approach, in line with the study protocol and with good practice in RCTs [70]. Missing data will be handled using either multiple imputation or Full Information Maximum Likelihood (FIML) method [71].

The primary analysis will consist of testing comparatively the magnitude of change in child aggresive behaviour, in the control vs. PLH-YC participants, at post-test and follow-up. Identical analyses will be run for the secondary outcomes (i.e. child internalising problems, dysfunctional parenting strategies, positive parenting, daily reports of effective parenting behaviour, child maltreatment, parental mental health, IPV, couple satisfaction, parenting stress, quality of parent-child relationship, and child ’s quality of life). The main analyses will involve testing pre-post or pre-follow-up differences controlling for pre-intervention levels whilst accounting for covariates. Maximum likelihood estimation with robust statistics will be used with Mplus 8.2 software to account for non-normal distributions in measures and also apply a FIML framework for handling missing data at post- or follow-up. The models will be further tested using latent growth curve models adjusting for country and pre-assessment levels of the outcome variables (e.g. age as a time-invariant covariate). Indirect effect models will be tested in a structural equation framework and include participation rate and fidelity as mediators for the PLH-YC group and enrolment rate as the mediator across groups. In additional analyses, we will also model the effects of participation (i.e., attendance). This will be analysed with Complier Average Cause Effect models that estimate the magnitude of the paths based on the baseline scores in predictors (e.g. family adversity) and actual participation [72]. Further clustering will be within groups (facilitators) and included in subsequent analyses as needed. The analyses for MINI-KID ODD/CD positive screen will be conducted with logistical regression models due to the categorical nature of the data. Depending on the distributions and on other descriptive indicators, Bayesian analyses will be used as deemed appropriate.

